# Inhaled aviptadil for the possible treatment of COVID-19 in patients at high risk for ARDS: study protocol for a randomized, placebo-controlled, and multicenter trial

**DOI:** 10.1186/s13063-022-06723-w

**Published:** 2022-09-20

**Keywords:** Aviptadil, VIP, COVID-19, ARDS, SARS-CoV-2

## Abstract

**Background:**

Despite the fast establishment of new therapeutic agents in the management of COVID-19 and large-scale vaccination campaigns since the beginning of the SARS-CoV-2 pandemic in early 2020, severe disease courses still represent a threat, especially to patients with risk factors. This indicates the need for alternative strategies to prevent respiratory complications like acute respiratory distress syndrome (ARDS) associated with COVID-19. Aviptadil, a synthetic form of human vasoactive intestinal peptide, might be beneficial for COVID-19 patients at high risk of developing ARDS because of its ability to influence the regulation of exaggerated pro-inflammatory proteins and orchestrate the lung homeostasis. Aviptadil has recently been shown to considerably improve the prognosis of ARDS in COVID-19 when applied intravenously. An inhaled application of aviptadil has the advantages of achieving a higher concentration in the lung tissue, fast onset of activity, avoiding the hepatic first-pass metabolism, and the reduction of adverse effects. The overall objective of this project is to assess the efficacy and safety of inhaled aviptadil in patients hospitalized for COVID-19 at high risk of developing ARDS.

**Methods:**

This multicenter, placebo-controlled, double-blinded, randomized trial with 132 adult patients hospitalized for COVID-19 and at high risk for ARDS (adapted early acute lung injury score ≥ 2 points) is conducted in five public hospitals in Europe. Key exclusion criteria are mechanical ventilation at baseline, need for intensive care at baseline, and severe hemodynamic instability. Patients are randomly allocated to either inhale 67 μg aviptadil or normal saline (three times a day for 10 days), in addition to standard care, stratified by center. The primary endpoint is time from hospitalization to clinical improvement, defined as either hospital discharge, or improvement of at least two levels on the nine-level scale for clinical status suggested by the World Health Organization.

**Discussion:**

Treatment strategies for COVID-19 are still limited. In the context of upcoming new variants of SARS-CoV-2 and possible inefficacy of the available vaccines and antibody therapies, the investigation of alternative therapy options plays a crucial role in decreasing associated mortality and improving prognosis. Due to its unique immunomodulating properties also targeting the SARS-CoV-2 pathways, inhaled aviptadil may have the potential to prevent ARDS in COVID-19.

**Trial registration:**

ClinicalTrials.gov, NCT04536350. Registered 02 September 2020.

**Supplementary Information:**

The online version contains supplementary material available at 10.1186/s13063-022-06723-w.

## Administrative information

Note: the numbers in curly brackets in this protocol refer to SPIRIT checklist item numbers. The order of the items has been modified to group similar items (see http://www.equator-network.org/reporting-guidelines/spirit-2013-statement-defining-standard-protocol-items-for-clinical-trials/).

## Introduction

### Background and rationale {6a}

The world has been experiencing an exceptional state, due to the SARS-CoV-2 pandemic. In the beginning of 2020, about 20% of individuals with the SARS-CoV-2 associated corona virus disease (COVID-19) suffered from a severe course, characterized by significant respiratory symptoms including the potentially lethal acute respiratory distress syndrome (ARDS) [1]. Since then, numerous studies have been initiated in order to evaluate therapeutic agents for the treatment of COVID-19. To date, an improved outcome in hospitalized patients has been shown in randomized controlled trials for anti-cytokine monoclonal antibodies (tocilizumab), Janus kinase inhibitors (baricitinib), and dexamethasone [2–4], which is reflected in current treatment recommendations by national and international health organizations and societies [5–8].

Further available therapy options for early outpatient treatment in high-risk patients include the monoclonal antibodies sotrovimab and bebtelovimab, antiviral substances remdesivir, nirmatrelvir/ritonavir, and molnupiravir, as well as inhaled corticosteroid budesonide and serotonin reuptake inhibitor fluvoxamine [9–14]. The monoclonal antibody combination casirivimab/imdevimab had been effective in reducing hospitalization risk and mortality till late 2021 but proved to have no benefit for the treatment of the emerging omicron variant [15]. At the time of setting up this study, other approaches like convalescent plasma, further antiviral antibodies and other experimental substances are being investigated [3, 16–18].

Despite the fast establishment and adaptation of recommendations for the clinical management of COVID-19, as well as large-scale vaccination campaigns, severe disease-courses still represent a threat, especially to patients with risk factors such as old age, arterial hypertension, or diabetes mellitus [19]. This indicates the need for alternative strategies to prevent and ameliorate respiratory complications associated with COVID-19, in order to effectively prevent intensive care (ICU) admissions and reduce mortality.

The results of the RECOVERY trial indicate that an excessive inflammatory reaction plays an important role in the pathophysiology of severe COVID-19 and the progression to ARDS [2]. In fact, severe cases of COVID-19 are associated with elevated serum levels of pro-inflammatory mediators [1, 20, 21]. SARS-CoV-2 specifically targets the surfactant-producing pulmonary alveolar type II (ATII) cells by binding to their angiotensin converting enzyme 2 (ACE2-) receptors and entering the cell [22]. Viral replication and infection of adjacent ATII cells then lead to a massive cytokine release and, consequently, to apoptosis and a critical decrease of surfactant production, which disrupts the alveolar gas exchange resulting in ARDS [22, 23].

Vasoactive intestinal peptide (VIP), a gut peptide hormone containing 28-residue amino acid peptides, was discovered and first synthesized in the seventies [24–26]. Next to fulfilling various effects in the nervous, digestive, cardiovascular, respiratory, and reproductive systems, VIP is physiologically highly localized in the lungs [27, 28]. There, it binds with ATII cells via the VPAC1 receptor, the same cell type to which the SARS-CoV-2 virus binds via the ACE2-receptor [22, 27]. When VIP binds to the ATII-cells, it inhibits NMDA-induced caspase-3 activity inside the cell, which in turn decreases production of the pro-inflammatory cytokines interleukin-6 and TNF-alpha [29–33]. It has been proposed as a modulator of lung inflammation and airway constriction [25, 26, 34], and its protective effects on pulmonary tissue have been shown in numerous animal models of lung injury in rats, guinea pigs, dogs, and sheep [35–37]. VIP was also shown to increase surfactant production by upregulation of choline phosphate cytidylyltransferase and C-Fos protein expression in ATII cells [38–40]. Recent data demonstrated that plasma levels of VIP are higher in patients with severe COVID-19, compared to healthy individuals and those with mild COVID-19 [41, 42], and that VIP can block SARS-CoV-2 virus replication in vitro [32].

Aviptadil, a synthetic form of VIP, might prevent COVID-19 patients from developing ARDS due to the above described anti-inflammatory properties. The presumed primary therapeutic mechanism of action of inhaled aviptadil is a combination of anti-inflammatory properties and induction of tolerogenic immune response of immune cells localized in the lungs [43, 44]. It has been shown to reduce interferon producing T cells, to dampen Th17-T-cells and to promote regulatory T-cells [43, 45, 46]. These immune-dampening effects have been previously described to occur in the alveolar compartment of sarcoidosis patients after inhalation of aviptadil, which demonstrates that its local application by inhalation is feasible and results in relevant immunological changes [43]. There is further promising evidence from a case report of a patient with pneumonitis resulting from check-point-inhibitor therapy for melanoma, in which the administration of inhaled aviptadil was well tolerated and led to dampening of alveolar inflammation, radiological and clinical improvement [47].

To date, there is no clinical evidence for the efficacy of inhaled aviptadil in COVID-19. However, it was recently observed in vitro that VIP can inhibit SARS-CoV-2 replication and reduce cellular proinflammatory cytokine production [32]. Two phase II trials have been announced recently on the US National Library of Medicine platform “ClinicalTrials.gov” (COVID-AIV (NCT04311697), AVICOVID-2 (NCT04360096)), which investigate aviptadil in patients with COVID-19 in the USA. Preliminary results of the COVID-AIV trial, which has been recruiting patients with COVID-19 and respiratory failure, indicate a promising antiviral effect of the intravenous administration of aviptadil [42]. In contrast, this current trial investigates the inhaled application of aviptadil in an earlier stage of disease, in patients at increased risk for ARDS. Inhaled aviptadil likely circumvents several potential side effects, like hypotension and tachycardia [43, 47].

Daily doses of up to 300 μg inhaled aviptadil have been shown to be safe in phase II trials for the treatment of sarcoidosis and pulmonary hypertension, as well as in a recently published phase I trial in the treatment of ARDS [43, 48–50]. Aviptadil has been given Orphan Drug Designation in the European Union and the USA for the treatment of ARDS and the inhaled application has been observed to be safe without severe side effects [43, 47, 51].

### Objectives {7}

The primary objective of this trial is to investigate the efficacy and safety of inhaled aviptadil in hospitalized COVID-19 patients at high risk for developing ARDS. The study will assess whether patients with COVID-19 under high risk for developing ARDS recover faster when they receive inhaled aviptadil in addition to standard care, compared to patients receiving standard care only. A secondary objective is the investigation of the overall course of disease under inhaled aviptadil in terms of need for mechanical ventilation, time requiring oxygen supplementation, infection-related biomarkers, and subjective severity of symptoms. The safety objective is to assess any potential harm of inhaled aviptadil.

### Trial design {8}

This study is a multicenter, placebo-controlled, double-blinded, randomized phase II trial with 132 adult patients. In a parallel group design, patients will be randomly allocated in a 1:1 ratio to inhale either aviptadil (67 μg three times a day) or normal saline (1 ml three times a day) for 10 days, or until hospital discharge, in addition to standard care. The study is conducted as a superiority trial.

### Public and patient involvement in the design of this protocol

Due to the novelty of the disease under investigation and the prevalent time pressure in the design phase of the trial, patient and public involvement in the design of this protocol was not applied.

## Methods: participants, interventions, and outcomes

### Study setting {9}

Recruitment of hospitalized patients takes place at the Cantonal Hospitals of Liestal and St. Gallen and the Hospital Schwyz in Switzerland, as well as the Clinic Hietzing, Vienna in Austria and the Antonius Hospital Nieuwegein in the Netherlands between May 2021 and December 2022 (estimated).

### Eligibility criteria {10}

Hospitalized patients with diagnosed COVID-19 are asked to take part in this study when the following eligibility criteria are fulfilled:▪ SARS-CoV-2 infection, verified according to current in-house guidelines▪ High risk for the development of ARDS:i.e., within 24 h before inclusion at least 2 points on an adapted EALI (early acute lung injury) score, with at least one point from the original EALI score [52, 53]Original EALI score:◦ 2–6 l O_2_ supplementation to achieve a SaO_2_ > 90%: 1 point◦ > 6 l O_2_ supplementation to achieve a SaO_2_ > 90%: 2 points◦ Respiratory rate ≥ 30/min: 1 point◦ Immunosuppression: 1 pointModification adapting for risk factors for ARDS in COVID-19 affected patients [54]◦ Arterial hypertension: 1 point◦ Diabetes: 1 point◦ Fever > 39 °C: 1 point▪ Age ≥ 18 years▪ Ability to comply with the inhalation maneuver▪ Ability to understand the clinical trial and sign the informed consent

The presence of any of the following exclusion criteria will lead to exclusion of the patient:▪ Mechanical ventilation or intensive care treatment within current hospitalization▪ Nasal high-flow cannula or continuous positive airway pressure (cPAP) ventilation at time of inclusion▪ Inability to conduct inhalation therapy▪ Hemodynamic instability with requirement of vasopressor therapy▪ Severe comorbidities interfering with the safe participation according to the treating physician▪ Previous participation in this trial, or current participation in another interventional study▪ Pregnancy▪ Systemic immunosuppression for chronic underlying condition (corticosteroid treatment as part of “standard care” allowed)

“Drop-out” is defined as the patient’s withdrawal of consent at any time after inclusion into the study.

### Who will take informed consent? {26a}

After a patient is identified as a potential participant, a Good Clinical Practice (GCP)-trained physician from the study team will inform the patient personally about the trial and ask for written consent by signature on the informed consent form. Each potential participant will be informed that participation in the trial is voluntary that he/she may withdraw from the study at any time with no need of justification and that withdrawal of consent will not affect his/her subsequent medical assistance and treatment. Consent or assent from authorized surrogates is not intended, patients who are not able to understand the trial or sign the informed consent form of their own accord are excluded from participation.

### Additional consent provisions for collection and use of participant data and biological specimens {26b}

Additional collection and use of participant data and biological specimens are not intended.

### Interventions

#### Explanation for the choice of comparators {6b}

Due to the novelty of the investigated disease COVID-19, global guidelines or a clear definition of standard care are not available at the time of implementation of the study. Additionally, standard treatment strategies may change during the study period in accordance with new research findings. At each study center, there are internal written guidelines for the clinical management of hospitalized COVID-19 patients, depending on the severity of the case. At the time of implementation of the study, elements of the standard care used in the participating study centers include oxygen therapy, systemic glucocorticoids, remdesivir, tocilizumab, nutritive measures, and prevention and management of ARDS, bacterial superinfections, and sepsis, as well as thrombembolic, neurologic, cardiac, and renal complications. Since there is no clear definition of standard care to date, the only ethically justifiable comparator is the best available care, which is adapted throughout the trial according to the current state of research.

#### Intervention description {11a}

Patients in the intervention group inhale 1 ml aviptadil solution (67 μg/ml) three times a day (morning, noon, evening), while participants in the control group inhale 1 ml of NaCl 0.9% three times a day. In both groups, the respective treatment is given in addition to standard care and lasts for 10 days, or until hospital discharge, whichever occurs first. The study drug is administered with the M-neb® dose+mesh nebulizer MN-300/8 in both study groups, and each application will approximately last for 10 min.

#### Criteria for discontinuing or modifying allocated interventions {11b}

Dose or device modifications are not intended. If clinically indicated, treating doctors can stop the treatment with the study drug. Participants are given the possibility to withdraw from the study at any time. Treating physicians can independently decide about additional treatment options and concomitant medication can be re-evaluated and changed at any time of this trial. A termination of the supplementation is reported to the coordinating study center immediately.

#### Strategies to improve adherence to interventions {11c}

All participants are hospitalized and medication is administered by qualified ward personnel. Ward personnel is responsible that participating patients receive the study medication in a correct manner and each administration will be documented in the patient records. Any complication or non-adherence with the administration is reported as a note to file.

#### Relevant concomitant care permitted or prohibited during the trial {11d}

All treatments considered necessary by treating doctors are permitted and their use is recorded in the case report form. Because inhaled aviptadil does not reach the systemic circulation and is mainly metabolized in the lung, pharmacokinetic interactions with aviptadil are not expected. In order to account for potential bias, we aim to analyze data from patients, who received potentially biasing concomitant treatment (e.g., immunosuppressants or immunomodulators) in an adjusted manner (see Statistical methods for primary and secondary outcomes {20a}).

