## Statistical methods

### Statistical methods for primary and secondary outcomes {20a}

R will be used for all statistical analyses [59]. Primary and secondary endpoints will be summarized by group using descriptive statistics (mean ± standard deviation for normally distributed data, median and interquartile range for other continuous data, absolute and relative frequencies for categorical data). A log-rank test will be used to compare Kaplan-Meier curves for the primary endpoint “time to clinical improvement,” with failure to reach clinical improvement or death before day 28 being right-censored at day 28. Sensitivity analyses will be performed with “death” and “clinical improvement” as competing risks. For potential confounders that are not fully balanced by randomization, adjusted analyses for the primary outcome may be performed using Cox regression models to estimate hazard ratios with corresponding two-sided 95% confidence intervals to compare with the respective unadjusted Cox model. The proportionality assumption for the Cox proportional hazards models will be tested by assessing Schoenfeld residuals.

Treatment effects on binary secondary endpoints will be analyzed by means of chi-squared test, or Fisher’s exact test, in case expected sub-group size is smaller than five. For discrete secondary endpoints, group differences will be assessed using a Poisson or negative binomial regression, depending on the underlying distribution. Treatment effects on patient-reported severity of symptoms will be analyzed with an ordinal logistic regression and an additional longitudinal analysis with cumulative link mixed models. Effects on longitudinal changes in infection-related biomarkers will be assessed using mixed effect linear regression and analysis of covariance. Patient-reported impact on health at day 28 will be compared between the two groups by means of Student’s *T*-test, or Mann-Whitney-*U* test, depending on normality of the data.

All statistical tests will be performed using two-sided tests at the significance level 0.05. Detailed methodology for statistical analyses of the data collected in this trial is documented in a separate statistical analysis plan (SAP). The SAP is finalized before database closure and can be obtained from the authors upon reasonable request. A summary of the SAP is provided in Additional file 1.

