### Methods in analysis to handle protocol non-adherence and any statistical methods to handle missing data {20c}

The primary analysis will be done in the intention-to-treat population and safety analysis will be done on all patients who started their assigned treatment. The time to clinical improvement will be assessed after all patients will have reached day 28, with failure to reach clinical improvement or death before day 28 considered as right censored at day 28. Careful trial planning and conduct will minimize the occurrence of missing data as far as possible. In case of missing data, treating physicians are contacted with the aim to complete missing data from patients’ records. No data imputation is planned.

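### Adjusting for immunomodulators received during the trial conditions on a post-randomisation variable, so the supportive adjusted hazard ratio can be biased

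*Protocol article*

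**What the plan says.** The relevant statements in the protocol article are these.

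- **{11d}, concomitant care:** "All treatments considered necessary by treating doctors are permitted and their use is recorded in the case report form". To deal with potential bias, the section continues, "we aim to analyze data from patients, who received potentially biasing concomitant treatment (e.g., immunosuppressants or immunomodulators) in an adjusted manner", and it points to {20a} for the method.
- **{11b}, discontinuing or modifying interventions:** "concomitant medication can be re-evaluated and changed at any time of this trial".
- **{20a}, statistical methods:** "For potential confounders that are not fully balanced by randomization, adjusted analyses for the primary outcome may be performed using Cox regression models". The resulting HRs are to be compared with those of the unadjusted Cox model.
- **Primary analysis, {20a} and {20c}:** "A log-rank test will be used to compare Kaplan-Meier curves for the primary endpoint", and "The primary analysis will be done in the intention-to-treat population".
- **{6b}, comparators:** systemic glucocorticoids and tocilizumab are among the elements of standard care, which may differ by centre and change over time.
- **{6a}, rationale:** "The presumed primary therapeutic mechanism of action of inhaled aviptadil is a combination of anti-inflammatory properties".

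**The concern.** The adjustment variable in {11d} is medication received under care during the trial. Nothing there restricts it to medication in use at randomisation, and {11b} leaves it open to change throughout. A drug added because a patient is getting worse is part of what follows randomisation. Randomisation cannot balance it, and it can be a consequence of the assigned arm. The protocol supplies a plausible route: the study drug is presumed anti-inflammatory and is meant to prevent deterioration, so it may reduce the need for added immunomodulators.

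Conditioning on such a variable does two things. If the added drug works, adjustment removes the part of the arm's total effect that runs through its use. If sicker patients are more likely to receive it, adjustment also compares unlike patients. When aviptadil lowers use, it takes a higher severity to be treated in the aviptadil arm. Aviptadil patients are then sicker than controls among the treated, and also sicker among the untreated. Both strata tilt against aviptadil.

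The trigger in {20a} adds to this. On-trial use becomes systematically unequal between arms when the study drug changes the disease course, so a rule to adjust for whatever is unbalanced selects the situation in which adjustment is least valid. What is at stake is the reading of the supportive analysis: an adjusted HR printed beside an unadjusted one is easily taken as the better estimate, when here it may be the worse.

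**Working it through.** **The plan's own figures.** The article gives no figure on this point. Its sample size fixes the expected information and reproduces: (1.96 + 0.84)² / (log²(1.75) × 0.25 × 0.8) = 7.84 / (0.3132 × 0.2) = 125.2. Then 126 / 0.97 = 129.9, rounded up to 130, and 132 as a multiple of four. Expected events are about 101. None of this changes with the point raised here.

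**Simulation set-up (all parameters assumed, since the article gives no rates of use).** There are 200,000 patients per scenario, split 1:1.
- Severity u is standard normal and unobserved.
- Receipt of an immunomodulator M (yes/no): logit P(M = 1) = −0.8 + g·u + k·arm.
- Daily hazard of improvement: 0.06 × exp(log(HR_arm)·arm − 0.7·u + log(HR_M)·M), censored at day 28.
- With HR_M = 1.0, 77% of patients reach the endpoint when HR_arm = 1.00 and 83% when HR_arm = 1.75, close to the 80% in {14}.
- A Cox model is fitted with arm only, then with arm and M. HR above 1 favours aviptadil.

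| HR_arm | g | Use, control vs aviptadil | HR_M | Unadjusted HR | Adjusted for M |
|---|---|---|---|---|---|
| 1.00 | 1 | 34.1% vs 33.9% | 1.0 | 0.999 | 0.998 |
| 1.00 | 1 | 34.1% vs 22.1% | 1.0 | 0.999 | 0.942 |
| 1.00 | 2 | 38.0% vs 28.4% | 1.0 | 0.999 | 0.930 |
| 1.00 | 1 | 34.1% vs 13.3% | 1.0 | 0.999 | 0.901 |
| 1.00 | 2 | 38.0% vs 20.2% | 1.0 | 0.999 | 0.873 |
| 1.00 | 0 | 31.4% vs 18.2% | 1.3 | 0.972 | 0.999 |
| 1.00 | 0 | 31.4% vs 10.0% | 1.3 | 0.956 | 0.999 |
| 1.75 | 1 | 34.1% vs 33.9% | 1.0 | 1.554 | 1.574 |
| 1.75 | 2 | 38.0% vs 38.0% | 1.0 | 1.554 | 1.610 |
| 1.75 | 1 | 34.1% vs 22.1% | 1.0 | 1.554 | 1.483 |
| 1.75 | 2 | 38.0% vs 28.4% | 1.0 | 1.554 | 1.495 |
| 1.75 | 1 | 34.1% vs 13.3% | 1.0 | 1.554 | 1.415 |
| 1.75 | 2 | 38.0% vs 20.2% | 1.0 | 1.554 | 1.397 |

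**Reading the table.**
1. No effect, arm does not alter use: no bias (0.998).
2. No effect, arm lowers use and use follows severity: 1.00 becomes 0.94 or 0.93 for a moderate reduction, and 0.90 or 0.87 for a strong one. Simulation error does not explain this: with 200,000 × 0.774 = 154,800 events, SE(log HR) is about 2/√154,800 = 0.005. Setting HR_M to 1.3 leaves the adjusted values within 0.001.
3. Use unrelated to severity, but the drug works: adjustment turns 0.97 or 0.96 into 1.00. It removes the path through medication and so answers a different question from the intention-to-treat effect.
4. Conditional HR 1.75: the unadjusted 1.55 falls to between 1.40 and 1.50. The drop from 1.75 to 1.55 is not bias. It arises because the HR changes when severity is averaged over, which is also why the adjusted value rises slightly to 1.57 or 1.61 when arm does not alter use. Measured against those two values, the shift caused by arm-dependent use is somewhat larger than the comparison with 1.55 suggests.

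**Limits of the simulation.** M is a fixed yes/no indicator and not time-dependent. The null rows let arm change prescribing without changing time to improvement, a stylised case chosen because the right answer is then known to be 1.00.

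**The case against.** The strongest reply has four parts.

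**The primary result is safe.** The primary comparison is an unadjusted log-rank test in the intention-to-treat population. The adjusted Cox models are optional and are shown next to the unadjusted model. This stands in full. A reader might infer that the trial's main treatment effect is adjusted for on-trial medication; the article does not say so.

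**A baseline reading is possible.** {11d} defers to {20a}, whose language about imbalance after randomisation suits baseline variables. Eligibility {10} allows standard-care corticosteroids, so some use may precede randomisation, and adjusting for that would be sound. The covariate is not defined further, and the detailed analysis plan is not shown. This stands in part: the article does not commit to a fixed on-trial indicator. But its wording names medication received, in a section about care during the trial, without a baseline limit. That is a loosely fixed rule, not detail left for later.

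**Bias is conditional.** Prescribers are blinded {17a}, so arm can affect prescribing only through the clinical course, and local guidelines may determine much of the use. This stands: the adjusted HR can be biased, but need not be.

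**The size depends on assumptions, and no positive trial is shown to be reversed.** With about 101 events, SE(log HR) is about 2/√101 = 0.199, so nominal significance needs an HR of about exp(1.96 × 0.199) = 1.48. Harsher assumptions (use of 37% vs 17%, and patients needing rescue recovering at 0.3 times the hazard) move 1.25 to 0.96. But 1.25 has z = 0.223/0.199 = 1.1 and would not be a positive trial. With a direct effect of 1.4, 1.59 becomes 1.28: below 1.48, but in the same direction. A supportive model could lose nominal significance; the primary conclusion would not be reversed.

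**Conclusion.** The point holds for the supportive analysis. As worded, {11d} read with {11b} and {20a} allows the adjusted Cox model for the primary outcome to include medication started after randomisation, which is not a confounder and can depend on the assigned arm. If aviptadil lowers the use of these drugs and sicker patients receive them more often, the adjusted HR is pulled against aviptadil: from 1.00 to about 0.87 to 0.94 with no true effect, and from 1.55 to about 1.40 to 1.50 with a conditional HR of 1.75. These sizes are illustrative and rest on assumed use of 34% to 38% in controls and 13% to 28% on aviptadil. Without dependence of use on arm, there is no bias under the null.

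The documents do not support a claim that the primary test is biased, that the adjusted HR is certain to be biased, or that a positive trial would be overturned. Severity: should be fixed, since the remedy is simple and the stated reason for adjusting, to guard against bias, can work the other way.

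**What to change.** Reword {11d} and {20a} so that:

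1. Adjusted models for the primary outcome include only pre-specified variables fixed at or before randomisation, for example steroid or immunomodulator already in use at randomisation (yes/no).
2. Immunosuppressant or immunomodulator use that starts later is reported descriptively by arm.
3. Any model that conditions on on-trial use is labelled exploratory, with a note that its HR does not estimate the intention-to-treat effect.

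The primary log-rank test, the analysis population and the sample size of 132 stay as they are. The cost is a few sentences, plus confirming that the case report form separates use before from use after randomisation: {11d} says that use is recorded but does not mention start dates. Counting the start of an immunomodulator as an unfavourable outcome is not advised, because {6b} lists such drugs as part of standard care.
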